### Intervention

In this study, intervention group 1 will receive PA and PST, while intervention group 2 will only receive PA. Both groups will engage in the intervention program alongside their primary caregiver. The control group will not receive any intervention. Throughout this process, the child will continue with their existing treatment, and if applicable, the additional intervention will be implemented.

### Physical activity (PA)

The PA intervention program is based on the meta-analysis conducted by Kim et al. (2022) [6]. On the effects of PA in children and adolescents with ADHD. Specifically, we used the PA program (aerobic exercise and manipulative exercises) from the parent-involved intervention study by Kim et al. (2024) [23,33]. The PA program will be conducted over eight weeks, consisting of two weekly sessions. Each session will last for 90 minutes and include 30 minutes of manipulative exercises followed by 60 minutes of aerobic exercise. The intensity of the PA will be maintained at a moderate to vigorous level, as indicated by a modified Borg Scale rating of 5–7. The level of physical activity will be monitored using the ActiGraph wCT3x-BT (ActiGraph, Pensacola, FL, USA), and efforts will be made to maintain the intensity of moderate to vigorous activity. All sessions will occur in a group setting, with primary caregivers and parents participating. Detailed information about the PA program can be found in Table 1.

**Table 1 pone.0325669.t001:** Physical activity program.

Week	Type	Program Contents
1	manipulative	Rolling and receiving a ball, pushing and stopping a ball with the foot (1m), bouncing a ball in place, and throwing and receiving a ball (1m)
	Aerobic	Horse running, jumping with both feet, step exercises, 10 m shuttle run (10 repetitions) 2 sessions
2	manipulative	Rolling and receiving a ball, pushing and stopping a ball with the foot (2m), bouncing a ball while walking, and throwing and receiving a ball (1m)
	Aerobic	Alternating jumps, jumping with both feet, step exercises, 10 m shuttle run (11 repetitions), 2 sessions.
3	manipulative	Rolling and receiving a ball, pushing and stopping a ball with the foot (3m), bouncing a ball while walking (zigzag), throwing and receiving (1.5m)
	Aerobic	Horse running, jumping with both feet, step exercises, climbing, 10 m shuttle run (12 repetitions) 2 sessions
4	manipulative	Rolling a ball while moving and receiving, pushing a ball while driving and stopping, bouncing a ball while running, and throwing and receiving (2m)
	Aerobic	Alternating jumps, jumping with both feet, step exercises, and a 10 m shuttle run (13 repetitions) for 2 sessions.
5	manipulative	Rolling a ball while moving and receiving, pushing a ball while driving and stopping, bouncing a ball while crossing a balance beam, and throwing and receiving a ball.
	Aerobic	Jumping with both feet, climbing, sliding, egg laying, 10 m shuttle run (14 repetitions) 2 sessions
6	manipulative	Hitting a stationary ball (ground, T-ball), hitting a rolling ball, hitting a flying ball
	Aerobic	Jumping with both feet, climbing, sliding, egg laying, 10 m shuttle run (15 repetitions) 1 session
7	manipulative	Kicking a stationary ball, kicking a rolling ball, dribbling a ball while moving in a zigzag
	Aerobic	Zigzag running, 10 m shuttle run, single-leg, double-leg, horse, alternating jumps, climbing.
8	manipulative	Solo balloon volleying, returning flying objects, and balloon tennis
	Aerobic	Zigzag running, 10 m shuttle run, single-leg, double-leg, horse, alternating jumps, climbing.

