### Sample size

The sample size for this study was determined through statistical analysis using the G*Power 3.1 program. Based on the data analysis method, the test family was set to F-tests, and the statistical test was designated as ANOVA: repeated measures, within-between interaction. The effect size was determined according to Cohen’s method [26] and was set to 0.25, based on previous studies [27–29]. Initially, the significance level (α) was set at 0.05 for the sample size calculation. However, to account for multiple comparisons, the Bonferroni correction was applied, adjusting the per-comparison significance level to α = 0.0167. The statistical power (1-β) was set at 0.80, the number of groups at three, and the number of repeated measurements at three. Consequently, the required sample size was recalculated to be 45 participants (15 per group). To account for potential attrition, a 20% dropout rate was considered, based on rates observed in previous studies [30–32]. Therefore, the final total sample size was 54 participants, with 18 participants allocated to each group.

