### Psychological Skills Training (PST)

A PST program specifically designed for children with ADHD will be implemented, grounded in essential principles and evidence-based practices of PST. This program will incorporate routines, goal setting, positive self-affirmation, concentration training, and anxiety management techniques (see Table 2). The training aims to enhance attention and alleviate stress and anxiety, which are frequently linked to ADHD. Sessions will be conducted once a week for 50 minutes over 8 weeks, with both primary caregivers and their children participating together in the PST.

**Table 2 pone.0325669.t002:** The Psychological Skills Training Program.

Session (Week)	Program
1	About ADHD
2	The Importance of physical activity
3	Routines Setting
4	Goal Setting
5	Anxiety Control Training
6	Positive Self-Suggestion
7	Attention Focus Training
8	Review of Sessions 2–7

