### Statistical analysis

The normality of the primary variables will be assessed using the Shapiro-Wilk test, and homogeneity of variances will be evaluated using Levene’s test. If normality is satisfied, a repeated measures ANOVA will be performed to examine the main effects of time, group, and their interaction. Mauchly’s test for sphericity will be conducted, and if violated, the Greenhouse-Geisser correction will be applied. If the normality assumption is violated, non-parametric alternatives will be implemented. The Kruskal-Wallis test will be used for between-group comparisons at each time point, while the Friedman test will be applied for within-group repeated measures. To adjust for multiple comparisons, Bonferroni correction will be applied as needed to control for Type I error. If significant interaction effects are observed in the repeated measures analysis, post-hoc tests will be conducted. For parametric statistics, paired t-tests will be used to compare within-group differences over time, and independent t-tests will be performed to compare mean differences between groups at the same time points. For non-parametric statistics, the Mann-Whitney U test will be used to compare two groups at a specific time point, and the Wilcoxon signed-rank test will be employed to analyze within-group differences between two time points.

All data collected in this study will be analyzed using SPSS 26 statistical software. The five subscales and total score of the Wechsler assessment will be analyzed separately. Since multiple comparisons will be made, a multiple comparisons issue may arise. To address this, the Bonferroni correction will be applied, setting the significance level to 0.0167. For other variables, the significance level will be set to 0.05 for analysis.

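### PA is given in group sessions to both intervention arms, but the tests and sample size treat families as independent, so type I error is inflated if outcomes within a session group are positively correlated

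*Protocol article*

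**What the plan says.** **Delivery.** The Physical activity (PA) section states that "All sessions will occur in a group setting, with primary caregivers and parents participating". The programme runs for eight weeks with two 90-minute sessions a week. The Intervention section says that "intervention group 1 will receive PA and PST, while intervention group 2 will only receive PA", and "The control group will not receive any intervention". Group delivery of PA therefore applies to two of the three arms. For psychological skills training (PST), the article says only that it is held "with both primary caregivers and their children participating together in the PST".

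**Analysis.** The Statistical analysis section names a repeated-measures ANOVA for time, group and their interaction, with Kruskal-Wallis and Friedman tests if normality fails. After a significant interaction, "independent t-tests will be performed to compare mean differences between groups at the same time points", or Mann-Whitney tests in the non-parametric case. No session-group term appears.

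**Sample size.** The effect size "was set to 0.25, based on previous studies", and the calculation allows for multiplicity by "adjusting the per-comparison significance level to α = 0.0167". With power 0.80, three groups and three measurements, the article reports 45. After the dropout allowance, "the final total sample size was 54 participants, with 18 participants allocated to each group". No ICC or design effect is mentioned.

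**The concern.** Families who exercise together over 16 sessions (8 × 2), or 24 hours (16 × 1.5), may come to resemble one another in outcome, because they share peers, atmosphere and the way the sessions happen to go. If so, 18 families in a few session groups carry less information than 18 independent families. The planned between-group tests estimate their error only from variation between individual families. A session group that does unusually well or badly then shifts the arm mean by more than the standard error allows for.

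IG1 versus IG2 is the most exposed contrast because both arms are clustered. It is also the contrast that isolates what PST adds to PA, a benefit that the abstract says the study will show. With 18 families per arm there can be only a few session groups of any size, so one atypical group has weight.

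**Working it through.** **1. The plan's own figure.** Inputs from Sample size: f = 0.25, α = 0.0167, power 0.80, 3 groups, 3 measurements. Not stated, so assumed at the G*Power defaults: correlation between repeated measures 0.5, and sphericity.

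- λ = f² × N × m / (1 − ρ) = 0.0625 × 45 × 3 / 0.5 = 16.875
- df1 = (3 − 1)(3 − 1) = 4; df2 = (45 − 3)(3 − 1) = 84
- Power = 0.8145 at N = 45. The smallest adequate N is 44, which becomes 45 for equal groups.

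The stated 45 is reproduced with independent families and no design effect.

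**2. Design effect and standard errors.** Both the ICC and the number of families per session group (k) are assumed. DE = 1 + (k − 1) × ICC, applied to the intervention arms only. The ratio of true to planned standard error is √DE for IG1 versus IG2, and √((DE + 1)/2) for an intervention arm versus control. At ICC 0.05:

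| k | DE | SE ratio, IG1 vs IG2 | SE ratio, arm vs control |
|---|---|---|---|
| 6 | 1 + 5 × 0.05 = 1.25 | 1.12 | 1.06 |
| 9 | 1 + 8 × 0.05 = 1.40 | 1.18 | 1.10 |
| 18 | 1 + 17 × 0.05 = 1.85 | 1.36 | 1.19 |

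Actual two-sided error at nominal 0.05 is 2 × (1 − Φ(1.96 / SE ratio)). For IG1 versus IG2 this gives 0.080, 0.098 and 0.150. For an intervention arm versus control it gives 0.065, 0.074 and 0.101.

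**3. Simulation of the planned tests.** There were 20,000 null trials per scenario, with 18 families per arm and repeated-measures correlation 0.5. A shared session-group effect acted at both post-baseline visits in IG1 and IG2 and not in controls. Actual error at nominal 0.05, for session groups of 6 / 9 / 18:

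| ICC | Group-by-time interaction | IG1 vs IG2, t-test | IG1 vs control, t-test |
|---|---|---|---|
| 0.01 | 0.053 / 0.055 / 0.065 | 0.057 / 0.060 / 0.068 | 0.052 / 0.053 / 0.062 |
| 0.05 | 0.075 / 0.093 / 0.149 | 0.081 / 0.098 / 0.152 | 0.063 / 0.076 / 0.102 |
| 0.10 | 0.109 / 0.148 / 0.266 | 0.111 / 0.149 / 0.248 | 0.084 / 0.103 / 0.155 |

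At ICC 0 all three tests hold their level (0.048 to 0.051). At nominal 0.0167, the level used in the sample size, the interaction test at ICC 0.05 runs at 0.029 / 0.039 / 0.076. The simulated t-tests agree with the formula in step 2.

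**4. Sample size, approximate.** Multiply 15 by DE in each intervention arm, round up, and leave 15 controls. At ICC 0.05 this gives 2 × 19 + 15 = 53, 2 × 21 + 15 = 57 and 2 × 28 + 15 = 71, against 45 before dropout.

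**The case against.** **The size is unknown.** The article gives no ICC, no number of session groups and no group size, so every inflated figure depends on two assumed inputs. At ICC 0.01 with groups of 6 the interaction test runs at 0.053, which is practically nominal. The largest values need ICC 0.10 or one group of 18 per arm, and neither is documented. This stands. A reader might infer that the standard errors are certainly too small, but the text supports only the conditional statement.

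**PST.** A reader might also infer that PST is given to several families at once, or that families share the same leaders. The PST section says only that caregiver and child attend together, which a single family with one trainer would satisfy, and the article does not say who leads any session. Neither inference is supported. The point does not need them, because PA alone clusters both intervention arms.

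**Gatekeeping by the interaction.** The post-hoc t-tests follow only a significant interaction, so their stand-alone error rates are not those of the whole procedure. That is correct, and it is why the interaction is reported separately. The interaction test is itself inflated when the ICC is positive.

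**Matter for an analysis plan.** Sensitivity models are commonly left to a plan that is not shown here. But the article itself fixes named tests that do not match its own delivery format, so this is more than an omitted detail.

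**Comparison with controls.** The Study design section draws controls from families who could not take part in the programme, so that contrast is not randomised. A session-group term does not repair this, and passing a clustering check must not be read as doing so. This stands as a limit on the fix.

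**Conclusion.** The point holds in conditional form. It is certain from the text that PA is group-delivered in both intervention arms and not in the control arm, and that the named between-group tests and the sample size ignore this. How much it matters is not known. With an assumed ICC of 0.05 and groups of 6 to 18 families, the planned interaction test at nominal 5% runs at about 7.5% to 15%. IG1 versus IG2 is affected to about the same degree, and an intervention arm versus control less. At an assumed ICC of 0.01 the inflation is small. These figures also assume repeated-measures correlation 0.5 and a group effect that persists to the last visit. The remedy is cheap relative to the uncertainty that it removes, so the change is worth making.

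**What to change.** - State the number and size of the PA session groups, and record each family's group.
- Keep the main model. Add one prespecified sensitivity analysis with a random session-group effect in IG1 and IG2 only (a partially nested mixed model with small-sample degrees of freedom).
- If there are too few groups to estimate that effect, or only one per arm so that group and arm are fully confounded, recompute the intervals at fixed ICCs of 0.01, 0.05 and 0.10 and report them beside the main result.
- Describe as fragile any effect that depends on assuming independence. Do not set a pass/fail rule at a single ICC: nothing in the article favours one value, and such a rule would let the sensitivity analysis override the main model.

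The cost is one recorded variable and one extra analysis. The downside is wider intervals (at ICC 0.05, by a factor of 1.12 to 1.36 for IG1 versus IG2) and an imprecise random effect when groups are few, which is why this is a sensitivity analysis. No session or treatment content changes.

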### Psychological Skills Training (PST)

A PST program specifically designed for children with ADHD will be implemented, grounded in essential principles and evidence-based practices of PST. This program will incorporate routines, goal setting, positive self-affirmation, concentration training, and anxiety management techniques (see Table 2). The training aims to enhance attention and alleviate stress and anxiety, which are frequently linked to ADHD. Sessions will be conducted once a week for 50 minutes over 8 weeks, with both primary caregivers and their children participating together in the PST.

**Table 2 pone.0325669.t002:** The Psychological Skills Training Program.

Session (Week)	Program
1	About ADHD
2	The Importance of physical activity
3	Routines Setting
4	Goal Setting
5	Anxiety Control Training
6	Positive Self-Suggestion
7	Attention Focus Training
8	Review of Sessions 2–7

### Outcome measures

The final analysis will include data collected from a total of 54 children and their primary caregivers, with 18 children and their respective primary caregivers assigned to each of the two intervention groups and the control group: Intervention Group 1 (n = 36: 18 children, 18 parents), Intervention Group 2 (n = 36: 18 children, 18 parents), and the Control Group (n = 36: 18 children, 18 parents). Data from children and their primary caregivers will be analyzed separately.

The examiner will conduct the assessments while being blinded to the group assignment. Cognitive assessments will be administered by a certified clinical psychologist to quantitatively evaluate participants’ cognitive functions. Additionally, the physical activity level will be collected using the ActiGraph, and this data will be used to monitor the provided level of physical activity. The following assessment tools will be used for children with ADHD and their parents. For cognitive assessment, the Korean-Wechsler Intelligence Scale for Children, Fifth Edition (K-WISC-V) and the Visual-Motor Integration, Sixth Edition (VMI-6) will be used. For emotional assessment, the Revised Children’s Manifest Anxiety Scale (RCMAS) and the Children’s Depression Inventory (CDI) will be utilized. For behavioral assessment, physical activity levels will be measured using the Global Physical Activity Questionnaire (GPAQ). ADHD symptoms, social skills, and sleep quality will be evaluated using the Swanson, Nolan, and Pelham Questionnaire (SNAP), the Social Skills Rating System-Parent (SSRS-P), and the Korean Version of the Pittsburgh Sleep Quality Index (PSQI-K).

For primary caregivers, the assessment tools will include the GPAQ, the Parenting Stress Index-Short Form (PSI-SF), the Beck Anxiety Inventory (BAI), the Beck Depression Inventory (BDI), and the Korean Version of the Pittsburgh Sleep Quality Index (K-PSQI).

All groups will undergo three assessments for all measures except for the K-WISC-V. Intervention Groups 1 and 2 will be assessed before the intervention, immediately after the intervention (three months after the first assessment), and three months post-intervention. The control group will be assessed at baseline, after three months, and after six months. The K-WISC-V will be administered to all groups before the intervention and six months post-intervention. Detailed information about the outcome measures can be found in Table 3.

**Table 3 pone.0325669.t003:** outcome measures.

Participants	Variable	Clinical assessment items
**Children**	**Cognitive**	Wechsler Intelligence Scale for Children: WISC
		Visual-Motor Integration, Sixth Edition: VMI-6
	**Emotional**	Revised Children’s Manifest Anxiety Scale: RCMAS
		Children’s Depression Inventory: CDI
	**Behavioral**	Swanson, Nolan and Pelham: SNAP
		Social Skills Rating System-Parent: SSRS-P
		Korean Version of the Pittsburgh Sleep Quality Index: PSQI-K
		Global Physical Activity Questionnaire: GPAQ
**Parents**	**Emotional**	Parenting Stress Index-short form: PSI-SF
		Beck’s Anxiety Inventory: BAI
		Beck’s Depression Inventory: BDI
	**Behavioral**	Korean Version of the Pittsburgh Sleep Quality Index: PSQI-K
		Global Physical Activity Questionnaire: GPAQ

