## Materials and methods

### Study design

This prospective randomized controlled intervention received approval from the Institutional Review Board of Incheon St. Mary’s Hospital (OC24FISI0032) on April 22, 2024. The protocol complies with the Helsinki Declaration and Good Clinical Practice guidelines. Participants will be divided into three groups: intervention group 1 (PA and PST), intervention group 2 (PA), and a control group (no intervention).

Initially, the two intervention groups will be categorized by age. We will randomly assign 18 children and their parents to each group, resulting in 72 participants, using a random number generator (version 1.1). The control group will consist of 18 children and their parents (36 participants) selected from those unable to participate in the interventions but who could complete the assessments. Therefore, the total number of participants across all groups will be 54 children, 54 parents, and 108 individuals.

To enhance the robustness of the analysis and mitigate potential biases from participant dropout, an intention-to-treat (ITT) approach will be implemented. All randomized participants will be analyzed regardless of intervention adherence. Missing data will be managed using multiple imputation methods to preserve data integrity and minimize bias. Additionally, sensitivity analyses will be conducted to evaluate the potential impact of missing data on the study outcomes.

All participants in this study will continue to receive their existing medication treatments throughout the intervention period. Before proceeding with the assessments and interventions, the children and their parents will provide written informed consent. Recruitment and data collection began on May 31, 2024 and is expected to end on February 28, 2025. Data collection and results are expected to be completed by September 30, 2025. Details of the research procedure are presented in Fig 1.

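### The K-WISC-V retest is set at a time that matches no listed visit and is undefined for controls, so retest intervals could differ between the intervention groups and control

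*Protocol article*

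**What the plan says.** All of the assessment timing visible to us is in the Outcome measures section of the protocol article.

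- General rule: "All groups will undergo three assessments for all measures except for the K-WISC-V".
- Intervention groups 1 and 2 are assessed before the intervention, then "immediately after the intervention (three months after the first assessment), and three months post-intervention".
- Controls: "The control group will be assessed at baseline, after three months, and after six months".
- K-WISC-V: "The K-WISC-V will be administered to all groups before the intervention and six months post-intervention".

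Both programmes last eight weeks. For physical activity: "The PA program will be conducted over eight weeks, consisting of two weekly sessions". For psychological skills training: "Sessions will be conducted once a week for 50 minutes over 8 weeks". The Intervention section says that controls receive no intervention.

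The Study design section expects recruitment and data collection to end on 28 February 2025, and then states: "Data collection and results are expected to be completed by September 30, 2025". The Statistical analysis section plans post-hoc comparisons in which "independent t-tests will be performed to compare mean differences between groups at the same time points", and it analyses five Wechsler subscales and the total score separately.

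**The concern.** The K-WISC-V sentence gives one time for all groups, but measures it from an event that only two of the three groups experience. For those two groups the time lies three months beyond their last listed visit. For controls it cannot be dated at all, and the only six-month contact named for them counts from baseline.

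Staff working from this sentence could reasonably test intervention children six months after the programme and controls at their month-6 visit. Group membership would then be tied to the interval between the two tests. Wechsler scores can change with repeat exposure and with age, so part of any difference from control could reflect the interval rather than the intervention. This would touch all six Wechsler scores in both contrasts with control. A retest given at the wrong time cannot be cleanly repeated.

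**Working it through.** **Inputs.** From Outcome measures: the post visit is at month 3, follow-up comes three months later, control visits are at months 0, 3 and 6, and the K-WISC-V retest is six months after the intervention. From the two programme sections: eight weeks each. From Study design: 28 February 2025 and 30 September 2025. Conversion: 365.25 / 12 / 7 = 4.35 weeks per month, so 3 months = 13.0 weeks and 6 months = 26.1 weeks.

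**Step 1: the plan's own schedule.** Post visit at month 3 + 3 months = month 6. This equals the controls' last visit, so the listed schedule is aligned on the protocol's own clock.

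**Step 2: the K-WISC-V time taken literally.** Retest time = end of intervention + 6 months. The end of intervention can be read in two ways:

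- week 8, the programme length, if it starts at baseline: 8 + 26.1 = 34.1 weeks (month 7.8);
- month 3, where the visit immediately after the intervention is placed: 13.0 + 26.1 = 39.1 weeks (month 9).

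Neither equals a listed visit.

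**Step 3: retest gap between intervention groups and control, by reading.**

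| Intervention groups tested at | Controls tested at | Gap (intervention minus control) |
|---|---|---|
| week 34.1 | month 6 (26.1 weeks) | 34.1 − 26.1 = 8.0 weeks |
| week 39.1 | month 6 (26.1 weeks) | 39.1 − 26.1 = 13.0 weeks |
| month 6 | month 6 | 0 |
| month 9 | month 9 | 0 |
| week 34.1 | month 9 (39.1 weeks) | 34.1 − 39.1 = −5.0 weeks |

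In the first two rows the intervention groups' interval is longer by a factor of 34.1 / 26.1 = 1.31 or 39.1 / 26.1 = 1.50.

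**Step 4: the calendar.** Take a family enrolled, with baseline on the same day, on 28 February 2025.

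- Eight-week end: 25 April 2025; six months later is 25 October 2025.
- Month-3 end: 28 May 2025; six months later is 28 November 2025.
- Six months after baseline: 28 August 2025.

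Only the last falls before 30 September 2025. Counting back from 30 September, the literal timing fits families enrolled up to about 2 February 2025 (eight-week end) or about 30 December 2024 (month-3 end). The overrun therefore concerns roughly the last four weeks to two months of the enrolment window.

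**Step 5: groups 1 and 2.** Both programmes run eight weeks, so under any single reading the two intervention groups share the same retest interval.

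**The case against.** The K-WISC-V is expressly exempted from the three-assessment rule, so a separate time for it is not in itself a contradiction. The sentence applies one timing to all groups, and the plan to compare groups at common time points suggests that a common time was meant. The most natural explanation is a slip for six months after baseline, in which case no unequal interval exists. The schedule figure (Fig 1) is not available here and may settle the matter. The calendar dates are expectations, and the 28 February 2025 date covers recruitment and data collection together, so reading it as the last enrolment day is an assumption.

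Much of this stands. A reader might infer that the trial will compare Wechsler tests given 8 to 13 weeks apart. The documents do not support that: nothing places the controls' second K-WISC-V at month 6, and other readings give no gap or a gap of about 5 weeks in the other direction. A reader might also be tempted to quantify a bias from practice effects, or a loss of power from a fading effect. The documents give no practice gain, fade rate or persistence figure, so neither can be sized from them. The comparison of intervention groups 1 and 2, the only one that Study design describes as randomised, is untouched.

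What does not fall away is the sentence itself. The exemption explains why the K-WISC-V is given fewer times. It does not explain a date counted from an intervention that controls never receive. Even if Fig 1 shows a sensible time, the text would still disagree with it.

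**Conclusion.** The point holds as a conflict in stated timing with a conditional consequence. The K-WISC-V retest time matches no listed visit, cannot be dated for controls, and overruns the completion date for families enrolled late in the window. That six months after baseline fits both the visit schedule and the calendar suggests a slip but does not prove one.

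The gap of 8 to 13 weeks (about 34 to 39 weeks against 26) arises only if two things happen together: the intervention groups follow the text literally, and controls are tested at month 6. The lower end also assumes that the programme starts at baseline. In that case the Wechsler contrasts with control could be confounded with practice and maturation, by an amount that the documents do not allow us to size. The case for action rests on the contradiction and on how easily it is removed.

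**What to change.** Replace the K-WISC-V sentence with one that fixes a single elapsed time from baseline for all three groups, with the same visit window in each. The simplest choice is baseline and the final visit six months after baseline. Suggested wording: the K-WISC-V will be given to all three groups at baseline and at the final visit six months after baseline, within the same window in every group. On the protocol's own clock this needs no extra participants and no extra visit. Its cost is that, if later persistence was the real interest, cognition is measured earlier than intended.

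If a later test is truly intended, state it as the same time from baseline for controls as for the intervention groups, add that visit for all three groups, and move the completion date. In either case, check that Fig 1 agrees with the revised text.
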